# Vitamin D in pregnancy (GRAVITD) – a randomised controlled trial identifying associations and mechanisms linking maternal Vitamin D deficiency to placental dysfunction and adverse pregnancy outcomes – study protocol

**DOI:** 10.1186/s12884-023-05484-x

**Published:** 2023-03-15

**Keywords:** Vitamin D, Pregnancy, Pre-eclampsia, Foetal growth restriction, Gestational diabetes, Placenta

## Abstract

**Background:**

The prevalence of vitamin D deficiency is high among pregnant women. Vitamin D deficiency in pregnancy is associated with increased risk of adverse pregnancy outcomes especially complications related to placental dysfunction and insulin resistance. The objective of this study is to investigate if a higher dose of vitamin D supplementation in pregnancy reduces the prevalence of vitamin D deficiency and prevents adverse pregnancy outcome with special emphasize on preeclampsia, foetal growth restriction and gestational diabetes.

**Methods:**

GRAVITD is a double-blinded randomised trial with parallel groups where all pregnant women attending the free of charge national nuchal translucency scan programme in gestational week 10–14 at Randers Regional Hospital are invited to participate. Enrolment started in June 2020. Participants are randomised in a two armed randomization with a 1:1 allocation ratio into 1) control group – receives 10 µg of vitamin D or 2) intervention group – receives 90 µg of vitamin D. A total of 2000 pregnant women will be included. Maternal blood samples and questionnaires describing life-style habits are collected upon enrolment. For half of the participants blood samples and questionnaires will be repeated again in 3rd trimester. Blood samples will be analysed for 25-hydroxy-vitamin D using high-performance liquid chromatography coupled with tandem mass spectrometry. Upon delivery, placental tissue and umbilicalcord blood will be collected and information on maternal and fetal outcomes will be exstracted from medical records.

The primary outcomes are serum levels of 25-hydroxy-vitamin D ≥ 75 nmol/L and the rate of preeclampsia, foetal growth restriction and gestational diabetes. Secondary outcome includes identification and impact on placental functions related to vitamin D. A tertiary outcome is to initiate a cohort of children born from mothers in the trial for future follow-up of the effects of vitamin D on childhood health.

**Discussion:**

Provided that this trial finds beneficial effects of a higher dose of vitamin D supplementation in pregnancies, official recommendations can be adjusted accordingly. This will provide a low-cost and easily implementable adjustment of prenatal care which can improve health for both mother and child during pregnancy and beyond.

**Trial registration:**

ClinicalTrial.gov: NCT04291313. Registered February 17, 2020

## Background

Vitamin D deficiency is common among pregnant women worldwide with a reported prevalence of up to 92% in the most severely affected populations [1, 2]. Common causes include living in Northern countries at higher latitude and a darker skin tone [3–5]. Further, the growing prevalence of pregnant women with adiposity is disturbing in this context, as adiposity increases the risk of vitamin D deficiency [6]. Vitamin D status is a matter of concern in the clinical setting, as vitamin D deficiency appear to affect foetal growth trajectories, just as vitamin D deficiency is associated with an increased risk of pregnancy complications related to placental dysfunction. Vitamin D deficiency hence increases the risk of pre-eclampsia (PE), gestational diabetes (GDM), low birthweight and preterm birth [7–10]. Moreover, insufficient maternal vitamin D levels (25(OH)D) is associated with long-term health risks for the offspring [11]. In utero vitamin D exposure affects bone development and the strength of the tooth enamel [12, 13]. Previous studies also link exposure to low levels of vitamin D during intrauterine life to an increased risk of later disease including increased risk of asthma, type 1 diabetes, autism, schizophrenia, and multiple sclerosis in the offspring [10, 11, 14].

Since only 60–80% of maternal 25(OH)D is transferred to the foetus [15], the maternal serum 25(OH)D level needs to be ≥ 75 nmol/L to ensure that the foetus reaches a 25(OH)D level of at least 50 nmol/L. In earlier studies from Denmark, around 30% of pregnant women had aa 25(OH)D level < 50 nmol/L and as many as 70–88% of the pregnant women did not reach a serum 25(OH)D level > 75–80 nmol/L [5, 16] putting the foetus at risk of developing vitamin D deficiency. In a previous cohort study we characterized our present study population, i.e. women giving birth at Randers Regional Hospital, a hospital covering both urban areas, smaller cities and rural areas. Here we found that 10% of the participants had vitamin D deficiency (25(OH)D level < 50 nmol/L) and only 58% reached a sufficient 25(OH)D level of ≥ 75 nmol/L [17]. Notably, this was a study undertaken in the summer months and with a high adherence (86%) to the official Danish recommendations of a daily vitamin D supplement of 10 µg during the entire pregnancy. However, the officially recommended intake of 10 µg vitamin D daily is mainly based on a more than 35 year old small-scale study from Norway [18, 19] and does not take into account the nutritional differences between Denmark and Norway – e.g. a higher prevalence of fish consumption in Norway [20].

PE, one of the pregnancy complications most strongly associated with vitamin D status [7], affects 3–5% of all pregnancies worldwide and PE is still a major cause for maternal and perinatal morbidity and mortality [21, 22]. Danish registers find that 3% of all pregnancies are complicated by PE [23]. We found a similar but slightly higher prevalence in our previous study conducted in 2016–2017 as 4.1% developed PE [17].

In our previous study, around 10% of the children were born small for gestational age (SGA) (birthweight below the 10th percentile) [17]. If growth restriction occur during pregnancy this increases the risk of complications in the prenatal period [24], and also the risk of diseases later in life [24, 25]. Such increased risks for the child occur when the estimated weight of the foetus is -15% (i.e. < 10th percentile) below the appropriate weight for the gestational age (i.e. foetal weight between the 10th 90th percentile), the condition coined foetal growth restriction (FGR). The risk is even bigger if the weight of the foetus is -22% or more below appropriate weight, the condition coined intrauterine growth restriction (IUGR) [24]. In our previous study, we found that average vitamin D levels were reduced in women who had children with PE and IUGR albeit the difference were only significant in case of IUGR [17]. Such associations have also been found by others [9].

Today GDM is described as the most common metabolic disorder of pregnancy with an increasing prevalence, affecting around 7–10% of all pregnancies worldwide [26]. Moreover, the risk of developing GDM is correlated with increasing maternal age and a high pre-pregnancy BMI. These are factors that are also increasing globally among the pregnant population [27–30]. GDM is considered as an early marker of glucose intolerance, associated with both insulin resistance and impaired insulin secretion, thereby an increased risk of maternal and fetal adverse outcomes such as macrosomia, birth trauma, respiratory distress syndrome, jaundice, and hypoglycemia, an increased rate of delivery with cesarean section, preterm labor, FGR and PE. Furthermore, there is a higher risk of obesity and diabetes in later life both for these women and their children. Some studies suggested that vitamin D play a crucial role in maintaining normal glucose levels and reduces the extent of pathologies associated with insulin resistance [31, 32].

Although it is well known that vitamin D is important in pregnancy, there are still conflicting results on whether vitamin D supplementation can reduce the prevalence of pregnancy complications. In 2012, Hollis & Wagner [33] reported that an increased dose of vitamin D supplementation in pregnancy could improve birth outcomes and lead to a significantly decreased prevalence of hypertensive disorders in pregnancy in a randomised controlled trial. Similar results have since been found by others in relation to PE [34–37], GDM [37, 38] and foetal growth [34, 36], however others found no effect [39, 40]. One of the main weaknesses in previous trials is a small sample size leading to lack of statistical power. Compiling existing data is also troublesome due to a large variance in the method chosen for evaluation of 25(OH)D status in different study populations. Notably, significant differences occur among different methods for measuring 25(OH)D [41] and too few studies use the relatively expensive methods using high-performance liquid chromatography coupled with tandem mass spectrometry (HPLC–MS/MS) despite the fact that these methods are considered to be the gold standard for measuring 25(OH)D [41, 42]. Another challenge in previous studies with vitamin D is the administration and doses of vitamin D and the duration of the intervention, which differs a lot from study to study. Along with this, it is important to keep in mind when comparing different clinical studies that the study design should be comparable in order for the results to be comparable.

As vitamin D is generated in the skin, another major challenge when performing clinical studies is sunshine exposure, which varies a lot according to geography but also according to season [43]. This is also enhanced by differences in skin tone, which has a large impact on the ability to produce endogenous vitamin D in the skin. A well designed large randomised clinical trial, covering a long enrolment period to allow for seasonal variance, is lacking.

## Methods

### Study design/aim

The aim of this clinical trial is to investigate if a higher daily dose of vitamin D, than what is currently recommended in Denmark, can reduce the prevalence of the major pregnancy complications related to low vitamin D level in pregnancy, when initiated after pregnancy is determined (week 9 to 14).

The trial is a double-blinded randomised clinical trial with parallel groups and a two armed randomization with a 1:1 allocation ratio. Focus is on the pregnancy complications related to placental dysfunction – PE, FGR (≤ -15% of the appropriate weight for the gestational age) and GDM, in addition effects of placental function will also be investigated. Enrolment to the trial will take place over a 2.5–3-year time period covering both the summer and winter months in order to cover periods of different sunshine exposure and variance from year to year.

### Study settings

The trial is conducted at the Department of Gynaecology and Obstetrics, Randers Regional Hospital, Denmark.

### Participants

Pregnant women attending nuchal translucency scan in gestational week 11–14 as part of the national prenatal screening program at Randers Regional Hospital are invited to participate in the trial. The nuchal translucency scan is a part of the national prenatal screening program, which is offered to all Danish pregnant women and attended by 94% [44]. The screening program is free of charge. When they attend the nuchal translucency scan at the hospital they receive both orally and written information about the trial by a member of the research group. At Randers Regional Hospital there are around 2,200–2,400 childbirths annually. Women who agree to participate will give informed written consent before participation in agreement with The Declaration of Helsinki.

#### Exclusion criteria

Age < 18 yearsUnable to give written informed consent > 15 complete weeks pregnant at the time of the nuchal translucency scanDisturbances in calcium metabolismChronic kidney diseaseVitamin D treatment initiated by a physician

### Intervention

All pregnant women who agree to participate will be randomised in equal proportions to receive either an extra vitamin D supplement (80 µg) or a placebo tablet. The participants will all receive a prenatal multivitamin (Livol®) containing 10 µg of vitamin D, which is the current national recommendation for pregnant women in Denmark [18, 45]. Thereby, all participants as a minimum gets the recommended vitamin D supplementation and are not in a higher risk of vitamin D deficiency than what they are at baseline and if they do not participate in the trial. There will be two parallel groups in the trial receiving either 90 µg or 10 µg of vitamin D respectively (Fig. 1). The dose chosen for the intervention group (90 µg) is within a dose interval previously proven safe by others [42, 46, 47] and the dose is 10% below the current limit for what can be purchased in Denmark without a prescription. The vitamin D supplement tablet and the placebo tablet are identical in appearance and taste and contain exactly the same ingredients except from the cholecalciferol which is only in the vitamin D supplement tablet. The vitamin D supplement and the placebo tablets are packed in anonymized containers and provided with a unique number. Vitamin D supplements, placebo tablets and the prenatal multivitamin (Livol®) are provided by Orkla Care, Denmark. Vitamins for the remaining part of the pregnancy will be handed out at enrolment and the women will be instructed to take the vitamins daily until delivery.

**Fig. 1 Fig1:**
[figure not shown]
CONSORT flow diagram of the trial with intended numbers

#### Adherence

In order to monitor adherence in the trial, all participants will receive an email with a three-item adherence questionnaire 168 days after inclusion to the trial, which is around gestational week 36–37. They are asked whether they take the supplements every day or if they have forgotten to take them either a few times or for a longer period of time. Further, they are asked if they take the project supplement and the prenatal multivitamin or just one of them. If the questionnaire is not returned a reminder will be sent out after five days and again after 10 days.

#### Concomitant care

The participants are not allowed to take other vitamin D containing supplements than those handed out as part of the intervention. At the time of enrolment participants will be thoroughly informed about this. Further, it is recommended that all participants continue to take a 40–50 mg iron supplement from week 10 in pregnancy (not handed out by the study group), as the recommendations for pregnant Danish women prescribe. The prenatal multivitamin handed out in this trial contains 27 mg of iron, but since this multivitamin also contains 400 mg of calcium, the iron in the tablet is poorly absorbed. Therefore, a recommendation to the participants will be to take a separate daily iron supplement and to ingest this supplement at least 3 h apart from the supplements handed out in this trial.

### Outcome

#### Primary

The incidence of PEThe incidence of FGR (defined as a negative deviation of more than 15% (10th percentile) from the expected foetal weight diagnosed at ultrasonography scans)The incidence of GDM (defined as 2-h plasma glucose ≥ 9 mmol/l following a 75 g oral glucose load)Maternal serum-25(OH)D > 75 nmol/L

#### Secondary

BirthweightSize related to gestational age (Small for Gestational Age; SGA, Appropriate for Gestational Age; AGA, Large for Gestational Age; LGA)The incidence of preterm birth (birth < 37 weeks of gestation)The incidence of postterm birth (birth > 40 weeks of gestation)The incidence of gestational hypertension (blood pressure > 140/90)Mode of deliveryThe incidence of infection during deliveryUse of antibiotics during labourAdmission rate to the neonatal wardThe incidence of postpartum haemorrhage (bleeding > 500 ml)APGAR score at 1, 5 and 10 min after deliveryIdentification of placental functions related to maternal vitamin D status especially those also related to vitamin D metabolism and pregnancy-complications

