#### Information from medical records

The following data will be collected from medical records:- Regarding pregnancy: duration of pregnancy, blood pressure (in 1st, 2nd and 3rd trimester, at delivery and after delivery), traces of glucose and protein in urine samples, the placement of the placenta, fetal growth and pregnancy related diseases.- Regarding delivery: mode of delivery, need of initiation of labour, need of oxytocin stimulation, use of analgesia, pyrexia during labour (defined as ≥ 38.2 °C with epidural, without epidural: ≥ 38 °C), use of antibiotics during labour, estimated volume of blood loss at delivery and 2 h postpartum, placental weight and need for caesarean section or assisted delivery.- Regarding the new-born: birthweight, sex, APGAR score at 1-, 5- and 10 min, admission to the neonatal ward, neonatal infection and malformations.

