### Statistics

#### Power calculation

There is no current information on what effect an increased vitamin D intake will have on the prevalence of preeclampsia or any of the other pregnancy complications of interest. Hence we have based our power calculation on a hypothesis of a 50–55% reduction in the prevalence of PE which we except to be the least common of the main targets, PE, FGR and GDM.

We expect a prevalence of PE of > 4% among the pregnant women getting the 10 µg vitamin D based on a prevalence of 4.1% in our previous study [17] with inclusion mainly during the summer months, hence the prevalence of PE will probably be a little higher when inclusion is done during both winter and summer months.

With a presumed prevalence of PE at > 4%, a significance level of 0.05 and a power of 80% then 1,000 women in each group will be sufficient to show a statistically significant difference between the two interventions despite a dropout of 5%. The entire study sample will be 2,000 women.

To test the hypothesis, that all participants in the intervention group reach a sufficient 25(OH)D level (≥ 75 nmol/L), a power calculation show that 15 women are needed in each group. The calculation is done with a power of 80% and a significance level of 0.05 and a presumed prevalence of 42% vitamin D insufficiency (25(OH)D < 75 nmol/L) before the intervention, based on data from our previous study [17]. Hence, we have chosen to take a second blood sample in the 3rd trimester in half of the cohort, resulting in 500 in each group.

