#### Statistical analysis

Data will be analysed according to intention to treat, but if there is a non-compliance and dropout of more than 10%, we will also perform the statistical analysis without those with non-compliance. Demographic data will be presented as counts and percentages for categorical variables and continuous variables will be presented as mean and standard deviation. Data will be tested for normality using QQ-plots and will be log transformed if applicable. For all statistical analysis a level of statistical significance will be defined as 0.05. The primary outcomes PE, FGR and GDM, will be assessed by comparing the event rates in the two groups using a chi-square test and results will be presented as absolute and relative risks along with 95% confidence intervals (Cl). A similar approach will be used for categorical secondary outcomes. A multiple linear regression model will be used to adjust for indifferences in baseline characteristics. The 25(OH)D level will be assessed by comparing the mean in the two groups using students t-test. The same approach will be used for continuous secondary outcomes. Linear regression models will be used to assess continuous variables such as serum levels, blood pressure and biological changes in the placentas.

Subgroup analysis will be performed for the following subgroups:25(OH)D level at enrolment (< 50, 50–75, > 75)Parity (nulliparous vs primiparous and multiparous)EthnicityBMI (Body Mass Index) (≥ 20- < 25, ≥ 25- < 30, > 30, > 35, > 40)Extreme weight gain during pregnancySmoking statusRelevant medicationSocio economic status (income and education)

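### The secondary outcome 'postterm birth' is cut at more than 40 weeks, which on either reading falls short of post-term, so most births it counts would be ordinary term births

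*Protocol article*

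**What the plan says.** The Secondary list under Outcome defines the two gestational-length outcomes next to each other. The first is "The incidence of preterm birth (birth < 37 weeks of gestation". The second, the item at issue, opens with "The incidence of postterm birth (birth" and, with its cut-off, reads "The incidence of postterm birth (birth > 40 weeks of gestation". Nowhere else does the article give another cut-off for post-term birth, a reason for choosing 40 weeks, or a weeks+days convention for this outcome.

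The source variable is in the list of data taken from medical records: "Regarding pregnancy: duration of pregnancy, blood pressure". For the analysis, after describing the chi-square test with absolute and relative risks for preeclampsia, FGR and GDM, the Statistical analysis section adds "A similar approach will be used for categorical secondary outcomes". The outcome will therefore be reported as an event rate per arm with risks and confidence intervals, under the label 'postterm birth'.

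**The concern.** The article dates pregnancy on the usual gestational scale. The Adherence section places a questionnaire sent 168 days (24 weeks) after inclusion at about week 36–37. That puts inclusion at about week 12–13 (36 − 24 = 12; 37 − 24 = 13), which agrees with the nuchal scan window. On that scale 40 weeks is the expected date of delivery, whereas post-term conventionally starts two weeks later. With preterm birth set below 37 weeks in the same list, the literal rule leaves 'term' ending on the due date.

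What is at stake is the meaning of the reported result. A reader of the trial report would take 'postterm birth' as an adverse outcome, while most of the women counted would have had ordinary term deliveries. The wording also leaves single cases open: a birth at 40+3 is an event if the rule means after 40+0, and not an event if it means more than 40 completed weeks.

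**Working it through.** The article states no post-term rate and no gestational-age distribution, so there is no figure of the plan's own to reproduce. The check has two parts.

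**1. Possible readings of the cut-off**

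- After 40+0: every birth past the due date counts.
- More than 40 completed weeks: births from 41+0 count. The Exclusion criteria do use completed weeks for the gestational-age limit, so this reading is possible, but the outcome list does not use those words.
- 42 completed weeks (42+0, 42 × 7 = 294 days): the usual meaning of post-term. This is the general obstetric convention and is not stated in the article.

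Neither reading of the printed rule reaches the third line.

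**2. How much the cut-off matters (illustration on assumed inputs)**

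Assumption: gestational age at birth is normal with mean μ = 39.5–40.1 weeks and SD σ = 1.2–1.7 weeks. Neither range comes from the documents. The share of births beyond cut-off c is 1 − Φ((c − μ)/σ).

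Example, μ = 39.5 and σ = 1.2:
- c = 40: z = 0.5/1.2 = 0.417, share 0.338
- c = 41: z = 1.5/1.2 = 1.25, share 0.106
- c = 42: z = 2.5/1.2 = 2.083, share 0.019

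At the four corners of the assumed range:

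| μ | σ | after 40+0 | after 41+0 | from 42+0 |
|---|---|---|---|---|
| 39.5 | 1.2 | 33.8% | 10.6% | 1.9% |
| 39.5 | 1.7 | 38.4% | 18.9% | 7.1% |
| 40.1 | 1.2 | 53.3% | 22.7% | 5.7% |
| 40.1 | 1.7 | 52.4% | 29.8% | 13.2% |

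The ranges are thus 34–53%, 11–30% and 2–13%. A slightly different assumed range (mean 39.3–40.0, SD 1.2–1.8) gives 28–50%, 8–29% and 1–13%, which leads to the same conclusion.

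Share of counted births that reach 42+0 (last column divided by the earlier one):
- Rule read as after 40+0: from 1.86/33.85 = 5% to 13.2/52.4 = 25%.
- Rule read as from 41+0: from 1.86/10.56 = 18% to 13.2/29.8 = 44%.

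So more than half of the counted births are not post-term under every combination tried and under either reading.

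In numbers of women: the Power calculation section says "The entire study sample will be 2,000 women" and allows 5% dropout, so about 2,000 × 0.95 = 1,900 births. That gives about 640–1,010 counted births after 40+0, 200–570 after 41+0, and 35–250 from 42+0.

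The normal curve is least reliable at 42 weeks. Induction shortens late pregnancies, so the 42+0 figures are probably too high. A smaller true tail would lower the share of counted births that are post-term and leave the direction unchanged.

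**The case against.** The strongest reply is that nothing in the trial's inference breaks. The same cut-off applies to both arms, so the chi-square comparison and the risks are valid for the event as defined. The outcome is one of about a dozen secondary outcomes, no power is claimed for it, and any cut-off can be applied later from data already extracted. The percentages rest on an assumed distribution. The full protocol or analysis plan, not shown here, may state the weeks+days convention. All of this stands, and it limits the point to a minor one. It does not excuse the printed definition, because the article fixes a specific number that does not fit the name given to it.

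Three stronger readings are tempting, and the documents do not support them.

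- A reader might infer that the outcome covers about half of all births. That needs both the wider reading (after 40+0) and the upper end of an assumed distribution. The article settles neither.
- A reader might infer that a change in induction practice, or a small shift in gestation, would create a false difference between arms. Under Randomisation and blinding, treating staff are blinded and containers are packed in balanced batches; the Discussion adds that the trial is single-centre with the same staff. A change in practice would reach both arms alike. If mean gestation differs between randomised arms beyond chance, that is a real treatment effect. The only error would be to describe it as an effect on post-term birth.
- A reader might infer that the result could not be compared with any other report of post-term birth. That is a claim about literature outside the documents and cannot be checked from them.

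**Conclusion.** The point holds as a mismatch between label and threshold. On either reading of more than 40 weeks, the outcome called 'postterm birth' would consist mainly of term births: under the assumed distributions, only about 5–25% of counted births reach 42+0 on the literal reading, and 18–44% if counting starts at 41+0. These figures depend on assumed means and SDs and on a normal upper tail that is probably too heavy. The qualitative conclusion needs only the convention that post-term starts at 42 completed weeks, and the fact that births between the printed cut-off and 42 weeks outnumber those beyond it.

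The validity of the randomised comparison is not in question, and neither the primary outcomes nor the sample size depends on this definition.

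**What to change.** Before unblinding, make one of two changes to the outcome list:

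- define post-term birth as birth at ≥42+0 weeks (≥294 days); or
- keep the present cut-off under an accurate name, such as 'birth after 40+0' or 'birth at ≥41+0', whichever was meant.

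In both cases state the cut-off in weeks+days. The two can also stand side by side as separately named outcomes.

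The cost is one line of text and no new data. The statistical price of the 42-week definition is a rarer event with a wider interval on the relative scale. As an illustration with 950 women per arm, two-sided 0.05 and 80% power, an assumed control rate of 45% allows detection of a fall to about 38.7% (relative risk 0.86), whereas an assumed rate of 5% needs a fall to about 2.6% (relative risk 0.51). That is acceptable for a secondary outcome for which no power is claimed.
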